**Methods and analysis:**

This study employs a hybrid type II implementation-effectiveness trial to evaluate the *TransformUs All Abilities* programme, targeting all government and independent, primary and secondary schools in Victoria, as well as special and mainstream secondary schools in Queensland and South Australia (n=2173 eligible schools). The effectiveness trial will focus on a subgroup of government/independent special schools for students with mild to moderate intellectual disability in Victoria, involving up to three intervention and three waitlist control schools (n=61 eligible schools). In both trials, outcomes will be guided by the RE-AIM framework focusing on reach, adoption and implementation (implementation trial) and effectiveness (effectiveness trial), with data collected at baseline and 6 months. The effectiveness trial will focus on students’ device-measured physical activity and sedentary behaviour—primary outcomes—and sleep, physical literacy and cognitive functions—secondary outcomes. Teacher feedback on the programme’s adaptation and their experience with programme implementation will also be collected, alongside qualitative feedback from a subsample of students regarding engagement/enjoyment and suggestions for improvements. Implementation data will be analysed descriptively and using linear mixed models to test changes over time. Effectiveness outcomes will be analysed using linear mixed models to compare intervention and waitlist control, accounting for confounding and school/classroom clustering. Interview data will be thematically analysed.

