#### Effectiveness trial

The effectiveness trial will be run in Victoria for practical reasons (ie, funding constraints regarding in-school data collection and professional learning sessions, and multiple ethics approvals that would be required from Departments of Education in different states/territories). Up to six Victorian special schools (up to n=3 intervention and n=3 waitlist control; out of n=61 eligible schools) will be recruited for the effectiveness trial. School staff in the intervention school will be offered at least one in-person professional development opportunity at their school. School staff will also access the *TransformUs All Abilities* training material, programme components and programme resources through the *TransformUs* website (https://transformus.com.au) and will be encouraged to use the strategies in their classrooms/school.

Intervention effectiveness will be assessed in relation to device-measured students’ physical activity and sedentary time (primary outcomes), sleep, physical literacy and cognitive functions (secondary outcomes), as well as teachers’ confidence and competence in implementing the *Transform All Abilities* programme (secondary outcomes). Teachers’ feedback on their experience of delivering the programme and the perceived barriers and facilitators to implementation will be sought with audio-recorded interviews/focus groups at the end of the trial. Additionally, at the end of the trial, we will conduct a 45 min focus group session with a small group of students at each intervention school to understand how students with disabilities view the opportunities for physical activity throughout the school day. With these discussions, we will aim to understand (1) students’ perceptions of the *TransformUs All Abilities* programme; (2) their enjoyment in relation to the programme and (3) perceived barriers and facilitators to the implementation of physical activity strategies in their schools.

The principal/nominated school leader will help to oversee the implementation of the intervention in the school. A nominated school contact/liaison will distribute information on the study for the purposes of recruiting staff and students for the evaluation and will help to coordinate the assessments when the research team visits the school.

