#### Effectiveness trial

Principals or nominated school leaders will receive an invitation for their school to participate in the effectiveness trial. After receiving informed principal consent, schools will distribute recruitment information to parents/children. Parental written/electronic consent for their child to participate in the study will be sought prior to the study commencement. In addition to the informed consent received from parents/guardians, verbal assent from students will be obtained prior to any student assessment through any communication means (eg, verbally or via alternative and augmentative communication). Allocation to intervention/wait-list control will be done pragmatically, based on schools’ preference.

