#### Effectiveness trial

For our primary outcome—ActiGraph-measured MVPA (min/day)—we are aiming to recruit a total of 134 students (intervention n=67; control n=67). Allowing for a 30% drop-out and incomplete data (accelerometer not worn for enough hours per day or days over the week), this would still give us a sufficient power to detect statistically significant differences in the primary outcome.

For data to be analysed with linear mixed models (additional details available in section ‘Data Analysis’), the fixed effects were estimated with an a priori power calculation using G*Power software. Assuming a moderate effect size (f² = 0.15), an α error probability=0.05, and power (1 – β error probability) = 0.80, and the group variable as predictor, fixed effects were estimated to require 55 observations. To account for the random effects of clustering (students in the same classroom), a design effect of 1.82 was estimated (based on a coefficient of variation of 0.15 and an average number of five students per classroom and a conservative Intraclass Correlation Coefficient value of 0.20), suggesting that 100 observations would be required (ie, 55×1.82 = 100). Accounting for 25% attrition, the final total sample size needed for the effectiveness trial is 134 participants (ie, 100 ÷ (1–0.25) = 134), from 27 classrooms (134 ÷ five students per class=27).

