### Data analysis

Qualitative information collected from the interviews and focus groups will be analysed using thematic analysis^67^ in NVivo V.14 (released in 2023, Lumivero). Using a hybrid inductive/deductive approach,^68 69^ we will code data inductively and categorise codes in themes according to common implementation outcomes (ie, acceptability, adoption, feasibility, fidelity, penetration, sustainability and satisfaction).^57^ Where coded quotes do not apply to any of the preconcerted themes, new themes will be created.

Quantitative data will be analysed using Stata V.18 (Stata Corp. LLP). Preliminary analysis will be conducted to describe the sample (demographic characteristics and distribution of the scores on the outcomes of interest). Teacher-level outcomes from survey and EMA text message responses—including current teaching practices, organisational readiness/climate, teacher’s competence/confidence, and perceived barriers and facilitators in implementation, as well as frequency and types of *TransformUs All Abilities* strategies implemented by teachers (ie, EMA responses)—will be summarised descriptively. Changes over time in those outcomes’ scores will be analysed using linear mixed models. For teachers in the implementation trial, we will use time as a predictor variable (baseline/follow-up for survey scores; multiple time points for EMA). For teachers participating in the effectiveness trial, the predictor of interest will be the interaction between study group (intervention/control) and time. All models will be adjusted for common confounders (ie, teacher’s age, sex, years of teaching experience) and controlled for the random effect of classroom as a clustering variable.

Student-level primary and secondary effectiveness outcomes will be analysed using separate linear mixed models to assess the fixed effects of the intervention (ie, study group [intervention/control] × time [baseline/follow-up]) on each continuous outcome (ie, physical activity, sedentary time, sleep, physical literacy and cognitive functions), adjusting for common confounders (ie, age, sex and student disability/functioning) and controlling for the random effects of clustering (ie, students in classrooms). The effects of an interaction term between study group, time and student disability/functioning will also be explored, to see whether different levels of support moderate the intervention effects.

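### Whole schools are allocated, at most three per arm, but the operative analysis and the sample size cluster on classroom only, so the primary test is anti-conservative unless schools do not differ in change

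*Protocol article*

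**What the plan says.** The protocol article describes the clustering of the effectiveness analysis in three places, and they do not agree.

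- Abstract, Methods and analysis: linear mixed models compare the arms, "accounting for confounding and school/classroom clustering".
- Data analysis, student outcomes: the fixed effect of interest is "study group [intervention/control] × time [baseline/follow-up"], and the model is described as "controlling for the random effects of clustering (ie, students in classrooms"). School appears neither as a random nor as a fixed effect.
- Sample size and power calculation, Effectiveness trial: the design effect of 1.82 is for students in the same classroom. There is no school component.

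The teacher models, in the same Data analysis section, are "controlled for the random effect of classroom as a clustering variable".

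The allocated unit is the school. Under Recruitment strategy: "Allocation to intervention/wait-list control will be done pragmatically, based on schools’ preference". Under Procedures and participants: "Up to six Victorian special schools (up to n=3 intervention and n=3 waitlist control; out of n=61 eligible schools"). The Strengths and limitations list says that schools may differ in capacity, resources and approach when they implement the programme.

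**The concern.** When whole schools are allocated, the error of the treatment contrast includes whatever makes pupils of one school change alike: the school leader, the professional development session, timetable, staffing and season. The protocol expects such variation between schools, but the model an analyst would follow has no term for it.

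The usual reassurance, that classroom is already a random effect, does not help here. A classroom or student intercept is constant over time, so it largely drops out of the difference between follow-up and baseline. What remains in the contrast is the school-by-time variation, divided by only three schools per arm. If the model leaves it out, the standard error is too small and the type I error exceeds 5%. At stake are the interval and p value of the primary outcome, and the power claim that rests on the same classroom-only assumption.

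**Working it through.** **1. The plan's own figure.** Inputs from Sample size and power calculation: f² = 0.15, "an α error probability=0.05, and power (1 – β error probability) = 0.80", one predictor, five students per classroom, coefficient of variation 0.15, ICC 0.20, attrition 25%.

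- F test with one predictor: N = 55 gives power 0.805.
- Design effect: 1 + ((1 + 0.15²) × 5 − 1) × 0.20 = 1.8225.
- 55 × 1.82 = 100.1, taken as 100.
- 100 ÷ 0.75 = 133.3, so 134.

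The stated 134 reproduces from its inputs. All of them are at classroom level.

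**2. Type I error of the group × time test with student and classroom intercepts.** Set total variance to 1. Take 50 analysed pupils and 3 schools per arm. Let r be the within-pupil correlation and v the school-by-time variance at each occasion. The documents give neither, so r = 0.6–0.7 and v = 0–0.05 are assumptions.

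- Variance the model reports: 4(1 − r)/50.
- True variance: 4[(1 − r − v)/50 + v/3].
- Actual alpha: 2{1 − Φ(1.96 × √(model variance ÷ true variance))}.

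Example with r = 0.65 and v = 0.02: the model variance is 4 × 0.35/50 = 0.0280. The true variance is 4 × (0.33/50 + 0.02/3) = 0.0531. The ratio is 0.528, its root 0.726, and 1.96 × 0.726 = 1.42, so alpha is about 15%.

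| v (share of total variance) | alpha, r = 0.6 | alpha, r = 0.7 | true SE ÷ model SE |
|---|---|---|---|
| 0 | 5.0% | 5.0% | 1.00 |
| 1% | 9.7% | 11.2% | 1.18–1.23 |
| 2% | 14.2% | 17.0% | 1.34–1.43 |
| 5% | 25.4% | 30.2% | 1.72–1.90 |

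A simulation under no effect (6 schools × 4 classes × 5 pupils, 5,000 runs, residual variance 0.4) gave:

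- 5.3% with only a stable school effect;
- 10.6%, 16.4% and 27.2% at v = 1%, 2% and 5%.

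A t test on school mean changes with 4 df stayed at 4.9–5.3% throughout.

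**3. A more favourable specification.** Suppose the classroom term did capture variation in change, so that the test were effectively one between classroom means. The inflation is then smaller but still present. In 20,000 runs, with the within-classroom correlation held at 0.20, type I error was 5.0%, 6.0%, 6.9%, 10.2% and 16.0% for a school ICC of 0, 0.01, 0.02, 0.05 and 0.10.

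**4. Power with schools as the unit.** f² = 0.15 in two equal groups is d = 2√0.15 = 0.775. With 100 analysed pupils in six schools (16.7 each), the design effect is 1.8225 + (16.7 − 5) × school ICC. The noncentrality is 0.775 × √(25 ÷ design effect), on 6 − 2 = 4 df (critical t 2.78).

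| assumed school ICC | design effect | power |
|---|---|---|
| 0 | 1.82 | 0.58 |
| 0.01 | 1.94 | 0.56 |
| 0.02 | 2.06 | 0.54 |
| 0.05 | 2.41 | 0.48 |
| 0.10 | 2.99 | 0.40 |

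The fall from 0.80 to 0.58 at ICC 0 comes from the 4 df alone. These figures take no credit for the baseline measurement.

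**The case against.** The best defence is that nothing shows schools will differ in change. At zero school-by-time variance a model with student and classroom intercepts keeps its 5% level. That stands. A reader might infer that the primary intervals are simply wrong. The documents give no school-level variance, so they support only the conditional statement and a range that starts at zero.

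A reader might also infer that the standard error could be too wide, if the model had a classroom intercept only and so treated a pupil's two measurements as unpaired. The documents do not support this. The section speaks of random effects in the plural, for students in classrooms, in a baseline/follow-up model. A student intercept is the natural reading, and spelling it out can be left to the analysis plan.

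For the teacher models, a reader might take classroom to be the same thing as teacher. The eligibility table recruits teachers and teacher aides, who may share a room, so the documents do not establish that. The allocation argument also does not reach the implementation trial, which has no comparison arm. What stands is that school is missing from the teacher models of the effectiveness trial.

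Two further points have force. The Timeline describes starts matched between intervention and wait-list schools, so calendar effects common to a pair would cancel, by an amount that cannot be judged from the text. And a full mixed model with six schools may be unstable.

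The issue cannot be put down to detail deferred to an analysis plan. Two current statements about the same analysis disagree, and the more detailed one omits the allocated unit.

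**Conclusion.** The point holds in conditional form. The abstract and the Data analysis section contradict each other on clustering, and the sample size follows the narrower version. As specified, the primary test is anti-conservative unless school-by-time variance is zero. Under the assumptions in the working, a variance share of 1–2% would raise type I error to two to three times nominal, and 5% to five or six times. The contradiction and the direction of the error are certain. The size is not, because it rests on an assumed school-by-time variance and within-pupil correlation.

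Copying the abstract's wording into the Data analysis section would not settle it. A plain school intercept is also constant over time and cancels from group × time in the same way. Nor does any clustering term remove confounding from allocation by preference.

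**What to change.** 1. In Data analysis, bring the student model into line with the abstract: random effects for student, classroom and school plus a school-by-time component, with small-sample degrees of freedom based on the number of schools.
2. Because that model may not be stable with six schools, name a school-level comparison of mean changes as the primary or confirming analysis: three against three on about 4 df, or a pair-based version if the matched starts are used. A paired analysis of three pairs would have 2 df.
3. Add the school level to the effectiveness-trial teacher models, without replacing classroom by teacher.
4. Restate the power in Sample size and power calculation with a school-level component and few degrees of freedom, giving the assumed school ICC and any gain claimed from baseline adjustment.

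The change needs no new data. Its cost is wider intervals and a less favourable power statement: about 0.40–0.58 for the stated effect size at a school ICC of 0–0.10, before any baseline gain, in place of 0.80.

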## Ethics and dissemination

### Ethics approvals and trial registrations

This research has received ethical clearance from the Deakin University Human Research Ethics Committee on 16 December 2021 (2021-368). Permission to conduct research in schools has also been provided by the Education Departments in Victoria (31 March 2023, ref. 2023-004726), Queensland (11 July 2022, ref. 550/27/2592) and South Australia (1 September 2022, ref. 2022-0020). Prospective trial registrations were completed for the implementation trial (ACTRN12622001082796; Universal Trial Number: U1111-1281-1103) and effectiveness trial (ACTRN12622001050741; Universal Trial Number: U1111-1280-8828) through the Australian New Zealand Clinical Trial Registry (ANZCTR) on 4 August and 28 July 2022, respectively. Voluntary opt-in informed consent is required to take part in this study. Eligible school staff can consent to take part in the implementation trial via the *TransformUs* website. For the effectiveness trial, school leaders must provide informed consent for their school to participate; schools will then seek written or electronic parental/carer consent for their child’s participation and students will provide verbal assent before any assessments. Examples of the participant consent forms are provided in online supplemental file 2. This research will be performed in accordance with the standards of ethics outlined in the Declaration of Helsinki.

### Data management

Audio recorded interviews/discussions will be transcribed verbatim and identifiable information will be removed prior to the analysis. Transcripts will be sent to participants to allow them to review or edit their responses (member checking). Physical activity, sedentary behaviour and sleep data will be downloaded from the accelerometers using ActiLife software and kept in shared folders only accessible by the research team. Data will then be processed in RStudio using the GGIR package.^71^ Published equations will be used to identify time spent in sedentary, light physical activity and MVPA during waking hours.^60 72 73^ Sleep will also be extracted based on previously published methods.^74^

### Dissemination

Plans for dissemination include sharing results with participating schools, parent groups and disability organisations through tailored summaries, presentations and accessible formats (eg, plain language reports, presentations at relevant non-scientific events and webinars). Participants and relevant representatives of the public will be consulted on preferred formats and timing for dissemination. Additionally, results will be disseminated with the wider scientific community via academic publications and conference presentations.
